#### Model development

We will develop a clinical prediction model for 30-day mortality using multivariable logistic regression with predictors that are deemed feasible. We consider predictors feasible when a parameter is available in at least 90% of the participants at the ED, reproducible and easily retrieved. Participants that are prospectively included in Zuyderland MC and MUMC+ will form the derivation cohort and their data will be used for model development. For external validation, we will retrospectively collect data of ED patients to form a validation cohort. For the development and validation of our model the Stiell criteria will be applied [46].

After external validation, we will test the predictive ability of the model for the secondary composite endpoint and test whether addition of clinical impression scores and/or non-routine laboratory tests results in a better prediction of adverse outcomes.

All data will be analysed using IBM SPSS Statistics for Windows, Version 24.0 (IBM Corp., Armonk, N.Y., USA) and R version 3.3.3.

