**Methods:**

The RISE UP study is a prospective observational multicentre cohort study in older (≥65 years of age) ED patients treated by internists or gastroenterologists in Zuyderland Medical Centre and Maastricht University Medical Centre+ in the Netherlands.

After obtaining informed consent, patients characteristics, vital signs, functional status and routine laboratory tests will be retrieved. In addition, disease perception questionnaires will be filled out by patients or their caregivers and clinical impression questionnaires by nurses and physicians. Moreover, both arterial and venous blood samples will be taken in order to determine additional biomarkers. The discriminatory value of triage- and risk stratification scores, clinical impression scores and laboratory tests will be evaluated.

Univariable logistic regression will be used to identify predictors of adverse outcomes. With these data we intend to develop a clinical prediction model for 30-day mortality using multivariable logistic regression. This model will be validated in an external cohort.

Our primary endpoint is 30-day all-cause mortality. The secondary (composite) endpoint consist of 30-day mortality, length of hospital stay, admission to intensive- or medium care units, readmission and loss of independent living.

Patients will be followed up for at least 30 days and, if possible, for one year.

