### Objectives and outcome

#### Objectives

Evaluation of the discriminatory value for adverse outcomes of:triage and risk stratification scores:Triage score: MTS [11]General risk stratification scores: APACHE II [13], ISAR score [6] and ISAR-Hospitalised Patients (ISAR-HP) score [39]Disease specific scores: Glasgow-Blatchford Bleeding Score (GBS) [40], abbMEDS score [14], Sepsis-related Organ Failure Assessment (SOFA) score [41] and Confusion, Urea, Respiration, Blood pressure, Age > 65 years (CURB-65) score [42]clinical impressions of nurses and physicians, SQ and disease perception of patientsroutine and non-routine laboratory resultsDevelopment and validation of a prediction model for short-term mortality and test the predictive ability of this model for the other adverse outcomes/endpoints

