### Study analysis

#### Statistical analysis

First, patients characteristics and outcomes will be described. Continuous variables will be reported as means with standard deviations or medians with interquartile range and categorical variables as proportions. Valid percentages will be used when values are missing.

Secondly, we will quantify the ability of the risk-stratification scores, clinical impression scores and non-routine laboratory tests to discriminate between the presence and absence of the different endpoints separately using the area under the receiver operator characteristics curve (AUC-ROC). We will determine their diagnostic accuracy using sensitivity, specificity, positive and negative predictive values (PPV, NPV), likelihood ratios and Youden’s index. For the discriminatory value of risk-stratification scores and clinical impression scores, combined data from both centres will be used. For the non-routine laboratory tests, only data from patients recruited in Zuyderland MC will be used.

Third, we will identify possible predictors of adverse outcome using univariable logistic regression analyses. Odds ratios (OR) with 95% confidence intervals (95% CI) will be calculated. Continuous variables will be checked for nonlinearity and collinearity. In case of missing items, we will use stochastic regression imputation to impute these items using predictive mean matching.

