#### Sample size calculation

Since we will be using logistic regression analysis to identify predictors of 30-day mortality, a minimum of 10 events per candidate predictor is suggested [47]. Expected 30-day mortality in older medical ED patients is assumed to be at least 10% based on previous studies in the Netherlands [4, 48]. Therefore, we decided to include 450 patients in Zuyderland MC and 150 patients in MUMC+ to form the derivation cohort. For external validation of our prediction model, we need approximately 100 events, and therefore, the sample size of the validation cohort will be based on the mortality rate of the derivation cohort (estimation: 800 patients).

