### Trial status

As of 22/12/2018, the study is still ongoing; we are about to finish the inclusion of patients for the validation cohort and are completing 1 year follow up. A total of 603 participants are included in the derivation cohort from July 2016 until the beginning of February 2017 in the two participating centres. In Zuyderland MC, 450 patients, and in MUMC+, 153 patients are included.

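### The mortality model's performance for the other adverse outcomes is assessed only on a composite that includes 30-day mortality, so that result alone cannot show that it predicts any non-fatal outcome

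*Protocol article*

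**What the plan says.** Model development fixes the outcome used for fitting: "We will develop a clinical prediction model for 30-day mortality using multivariable logistic regression with predictors that are deemed feasible". Under Objectives, once the model for short-term mortality has been developed and validated, the aim is to "test the predictive ability of this model for the other adverse outcomes/endpoints".

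The analysis given for that aim is in Model development: "After external validation, we will test the predictive ability of the model for the secondary composite endpoint". The same sentence goes on to adding clinical impression scores and non-routine laboratory tests to the model. No other endpoint for the model is named.

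The Outcomes section lists 30-day mortality as the first component of the composite, and the abstract agrees: "The secondary (composite) endpoint consist of 30-day mortality, length of hospital stay, admission to intensive- or medium care units, readmission and loss of independent living".

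The Statistical analysis section does plan an endpoint-by-endpoint assessment, "to discriminate between the presence and absence of the different endpoints separately". Its subjects are the risk-stratification scores, the clinical impression scores and the non-routine laboratory tests. The new model is not among them.

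**The concern.** The objective asks about outcomes other than the one the model was built on. The stated analysis mixes that outcome back in. A model that ranks deaths well will show some discrimination for any endpoint that counts those deaths as events, whether or not it carries information about the rest.

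The stakes are in interpretation. The Discussion foresees an online calculator, possibly built into electronic records, and the study's stated goal is a tool for adverse outcomes in general. A composite AUC above 0.5 could be taken as evidence that the calculator also flags patients who will stay long, need ICU/MCU care, be readmitted or lose independent living. The analysis as written cannot separate that from the contribution of the deaths.

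**Working it through.** **Inputs from the protocol article**
- 30-day mortality of at least 10% (Sample size calculation).
- Validation cohort: "For external validation of our prediction model, we need approximately 100 events", with an estimated 800 patients. Taken together these imply 100/800 = 12.5% mortality. At exactly 10%, 100 events would need 100/0.10 = 1,000 patients. The size is tied to the derivation cohort's mortality, which is not reported, so the 800 can be neither confirmed nor called wrong. Both 10% and 12.5% are used below.
- Derivation cohort: 603 patients, so about 60 deaths at 10%.

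**Assumptions (no figures in the document)**
- Composite event rate of 30–60%.
- Model AUC for death, A, of 0.70–0.85.
- Limiting case: among patients who survive, the score is unrelated to every non-fatal component.

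**Formula.** Draw one patient with the composite and one without. With probability w = deaths / composite events, the first is a death and has the higher score with probability A. Otherwise the first is a survivor with a non-fatal event, and the comparison is a coin toss. Hence

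composite AUC = w × A + (1 − w) × 0.5.

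**Central case.** Mortality 10%, composite rate 40%, A = 0.80:
- w = 0.10/0.40 = 0.25
- AUC = 0.25 × 0.80 + 0.75 × 0.5 = 0.200 + 0.375 = 0.575

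**Range**

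| Mortality | Composite rate | w | A = 0.70 | A = 0.80 | A = 0.85 |
|---|---|---|---|---|---|
| 10% | 30% | 0.333 | 0.567 | 0.600 | 0.617 |
| 10% | 40% | 0.250 | 0.550 | 0.575 | 0.588 |
| 10% | 50% | 0.200 | 0.540 | 0.560 | 0.570 |
| 10% | 60% | 0.167 | 0.533 | 0.550 | 0.558 |
| 12.5% | 30% | 0.417 | 0.583 | 0.625 | 0.646 |
| 12.5% | 40% | 0.313 | 0.563 | 0.594 | 0.609 |
| 12.5% | 50% | 0.250 | 0.550 | 0.575 | 0.588 |
| 12.5% | 60% | 0.208 | 0.542 | 0.563 | 0.573 |

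The range is about 0.53 to 0.65. A rarer composite gives deaths more weight: at 20% the same formula runs from 0.50 × 0.70 + 0.50 × 0.5 = 0.600 (10% mortality) to 0.625 × 0.85 + 0.375 × 0.5 = 0.719 (12.5% mortality).

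**With deaths removed.** Setting w = 0 gives 0.5, so the same uninformative model is correctly shown to have no discrimination for the non-fatal outcomes.

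**The case against.** **No test is stated.** The article gives no null hypothesis, alpha or AUC threshold for the model on the composite. Elsewhere it describes quantifying discrimination and accuracy, not passing a test. This stands. A reader might infer that the analysis will usually succeed, or attach a false-positive rate to it; the document supports neither. Its Background calls existing scores with AUCs of 0.59–0.74 inaccurate. Most values in the table lie within or below that range, so a model carried only by deaths would seldom look useful by the protocol's own yardstick.

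**The composite AUC is not biased for the composite.** This also stands. The composite is a defined secondary endpoint and can be read as an endpoint other than the primary one. What that reading cannot deliver is information on outcomes other than death, which the Objectives also name.

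**Including death has a stated reason.** The Discussion notes that some outcomes rule out others, as in-hospital death rules out readmission. That is a good reason to keep the composite. It does not make the composite informative about its non-fatal parts.

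**Component results are detail that an article may leave out.** This has some force, and the article does not say that the composite is the sole analysis. But it does name an endpoint for this objective, and that endpoint does not match the objective's wording.

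**A survivor analysis has faults of its own.** It conditions on something unknown in the ED and drops ICU/MCU admissions and long stays in patients who then die. Readmission is counted from discharge, so its window can run past day 30 from the visit, and survival to day 30 does not fully remove competing death. These points stand. They are why it should be labelled as conditional and shown beside component results.

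**Conclusion.** The objective and the analysis stated for it do not match. The composite AUC is sound as an estimate for the composite, but it contains the outcome used to build the model and cannot alone support a claim about long stay, ICU/MCU admission, readmission or loss of independent living. In the limiting case of no non-fatal association, deaths alone would give about 0.575 in the central setting and about 0.53–0.65 over the main range.

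These figures rest on assumed composite rates and assumed AUCs for death. The limiting case shows how much of the composite AUC deaths could supply; it is not a forecast that the model will fail for the other outcomes. The derivation and validation of the model for 30-day mortality are unaffected.

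**What to change.** In Model development:
1. Keep the composite analysis, and describe its AUC as including the outcome on which the model was built.
2. Add the model's AUC for each non-fatal component: stay over 7 days, ICU/MCU admission, unplanned readmission and loss of independent living. State for each how patients who die are counted.
3. Add the model's AUC for the non-fatal part of the composite among patients alive at 30 days, labelled as conditional on 30-day survival. Deaths are then neither events nor event-free controls.
4. Base any statement about the other adverse outcomes on items 2 and 3, read together.

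Cost: a small extra analysis on outcomes already being collected, and a few sentences of text. The survivor analysis leaves out about 10% of patients (80 of 800 at 10% mortality, 100 of 800 at 12.5%) and the non-fatal events of those who die. The added AUCs will probably be lower than the composite AUC.

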#### Sample size calculation

Since we will be using logistic regression analysis to identify predictors of 30-day mortality, a minimum of 10 events per candidate predictor is suggested [47]. Expected 30-day mortality in older medical ED patients is assumed to be at least 10% based on previous studies in the Netherlands [4, 48]. Therefore, we decided to include 450 patients in Zuyderland MC and 150 patients in MUMC+ to form the derivation cohort. For external validation of our prediction model, we need approximately 100 events, and therefore, the sample size of the validation cohort will be based on the mortality rate of the derivation cohort (estimation: 800 patients).

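### The derivation cohort meets the stated 10 events per candidate predictor only if candidates are held to about 6, but the plan states no number and sets no cap

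*Protocol article*

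**What the plan says.** The Sample size calculation in the protocol article starts from the rule that "a minimum of 10 events per candidate predictor is suggested". It adds a mortality assumption, "Expected 30-day mortality in older medical ED patients is assumed to be at least 10" per cent, and concludes: "we decided to include 450 patients in Zuyderland MC and 150 patients in MUMC+ to form the derivation cohort". The number of candidate predictors, the third quantity the rule needs, is not given. Trial status reports the achieved size: "A total of 603 participants are included in the derivation cohort".

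Under Statistical analysis, "we will identify possible predictors of adverse outcome using univariable logistic regression analyses". Neither a list nor a count of the variables entering this step is given. The abstract follows its own mention of the univariable step with: "With these data we intend to develop a clinical prediction model for 30-day mortality using multivariable logistic regression". Model development restricts the model by feasibility: "We consider predictors feasible when a parameter is available in at least 90% of the participants at the ED, reproducible and easily retrieved". That restriction carries no upper number.

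Objectives names routine and non-routine laboratory results among the things to be evaluated. Data collection and follow up lists the routine laboratory tests one by one, with vital signs, age and sex and much else. After external validation, the plan will also "test whether addition of clinical impression scores and/or non-routine laboratory tests results in a better prediction of adverse outcomes".

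**The concern.** An events-per-candidate rule gives a sample size only once the number of candidates is fixed. Here the size is presented as a consequence of the rule, yet the text leaves far more variables open than 600 patients can carry under it. A reader would reasonably take the paragraph as assurance that the model will not be badly overfitted. That assurance holds only for a short candidate list, and the article neither states the list's length nor limits it.

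If many more candidates are tried on about 60 deaths, the derived model will look more discriminating in its own data than in new patients. Its predicted risks will also be too spread out. The rule counts candidates, not retained predictors, so a short final model does not satisfy it if a long list was searched to find it.

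**Working it through.** **Inputs**

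- Rule: 10 events per candidate predictor (Sample size calculation).
- 30-day mortality: at least 10% (same section).
- Derivation cohort: 450 + 150 = 600 planned; 603 achieved (Trial status).
- Validation target: about 100 events in an estimated 800 patients (Sample size calculation), which implies 100/800 = 12.5% mortality.
- 3-month mortality in older medical ED patients: 23.8% (Background). This is a generous ceiling for a 30-day rate.
- Routine parameters in Data collection and follow up: 23 laboratory tests (glucose through activated partial thromboplastin time), 6 vital signs (blood pressure counted once), age and sex. Total 23 + 6 + 2 = 31.

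**1. The plan's own figure.** Required N = 10 × candidates / mortality. The candidate number is missing, so 600 cannot be derived from what is stated. Solved backwards, candidates = 600 × 0.10 / 10 = 6. Forwards, 6 × 10 / 0.10 = 600 exactly. The achieved 603 gives 60.3 deaths and the same limit of 6.

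**2. Candidates supported by 600 patients if mortality is higher**

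| 30-day mortality | Deaths in 600 | Candidates at 10 deaths each |
|---|---|---|
| 10% | 60 | 6 |
| 12.5% | 75 | 7 |
| 15% | 90 | 9 |
| 20% | 120 | 12 |
| 23.8% | 142.8 | 14 |

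**3. Deaths per candidate for sets the text leaves open**

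| Set | Number | At 10% | At 12.5% |
|---|---|---|---|
| Age, sex, vital signs | 8 | 60/8 = 7.5 | 75/8 = 9.4 |
| Routine laboratory tests alone | 23 | 60/23 = 2.6 | 75/23 = 3.3 |
| All of these | 31 | 60/31 = 1.9 | 75/31 = 2.4 |

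At 23.8% mortality the 31 would still have only 142.8/31 = 4.6 deaths each.

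**4. What the rule would require for 31 candidates.** 31 × 10 = 310 deaths: 310/0.10 = 3,100 patients at 10%, or 310/0.125 = 2,480 at 12.5%. With 600 patients, mortality would have to be 310/600 = 51.7%.

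The count of 31 omits comorbidity, cognition, prior visits, medication, impression items and non-routine tests. It also omits extra parameters for nonlinear terms, although the plan checks continuous variables for nonlinearity.

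**5. Added-value step.** Study blood samples are taken only in Zuyderland MC (Blood sample collection), so mortality analyses of the non-routine tests rest on about 450 × 0.10 = 45 deaths. The composite endpoint includes 30-day mortality and so has at least as many events.

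**The case against.** The strongest defence is that the stated arithmetic contains no error. Six candidates at 10% mortality need exactly 600 patients, so the sponsor may have had 6 in mind, and the list may stand in a fuller protocol or analysis plan. That is a fair possibility. It removes any charge of a wrong calculation, and the lack of a printed candidate list is not itself the point. What remains is that the article gives a sizing rule and a conclusion without the quantity linking them, and then describes a predictor analysis that does not keep to it.

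A reader might infer that the plan screens 31 candidates at 1.9 deaths each. The document does not support that. The 31 is a count of collected parameters, made before the 90% availability criterion is applied. The Discussion adds that specialists were consulted beforehand on meaningful predictors and that mostly morbid-state variables will be chosen. These steps do not use outcome data and may shorten the list considerably. They set no cap, however, and age, sex and vital signs alone already exceed 6.

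A reader might also infer that univariable p-values decide entry to the model. The abstract's sequence suggests a link, but no selection rule is stated, and the univariable step may serve only the separate aim of identifying predictors. For the added-value step, nothing says that all non-routine tests are entered together, so an events-per-parameter figure for a joint refit would be invented.

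Finally, external validation with about 100 events is planned, and the Discussion makes the online calculator conditional on its success. This limits the harm: validation can expose overfitting, but it does not prevent it.

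**Conclusion.** The point holds in a limited form. On the plan's own figures, the derivation cohort supports about 6 candidate parameters at 10% mortality, 7 at 12.5%, and 14 at a rate that is almost certainly too high for 30 days. The predictor analysis as described leaves at least 31 routine parameters open. The stated criterion is therefore met only if candidates are held to about 6, and the text does not do this.

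The limit of 6 rests only on the plan's rule, mortality and sample size. Because mortality is given as at least 10%, 60 deaths is a floor, but no plausible rate supports 31 candidates. The figure of 1.9 deaths per candidate is conditional on all 31 being candidates. It marks the lower end for this routine set and does not describe what will be done. How far performance would be overstated cannot be computed from the article, because it states neither the candidate list nor the selection procedure.

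**What to change.** In the Sample size calculation, state that 600 patients support about 6 candidate parameters at 10% mortality, counting nonlinear terms. Then choose one of two routes.

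- Prespecify a list of that size on clinical and feasibility grounds, before any outcome associations are examined.
- Keep a larger set and state the actual events per candidate. Fit with penalisation or shrinkage, repeat every selection step inside a bootstrap, and report optimism-corrected AUC and calibration slope.

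Under either route, say that univariable odds ratios are descriptive and do not select predictors.

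For the added-value step, hold the final model's linear predictor fixed and add markers to it in the patients who have them. Give the number of events for the endpoint used. Label any extension not tested in the retrospective validation cohort as not externally validated. This is likely to matter because the article's other retrospective sample, described under Possible selection bias, omits questionnaires and non-routine tests.

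The cost is plan wording and some analysis code. Recruitment of the derivation cohort is complete, and no further patients are needed. The drawback is a shorter candidate list or a shrunken model, with a less favourable apparent AUC.

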### Trial status

As of 22/12/2018, the study is still ongoing; we are about to finish the inclusion of patients for the validation cohort and are completing 1 year follow up. A total of 603 participants are included in the derivation cohort from July 2016 until the beginning of February 2017 in the two participating centres. In Zuyderland MC, 450 patients, and in MUMC+, 153 patients are included.

